## Methods

### Study Design

This is a 6-week pilot study to examine the feasibility, acceptability, and usefulness of a co-designed VR exergame intervention among older adults as well as the feasibility of the study procedures and assessment protocol. A control group will be used to account for practice and exposure effects and will follow the same protocol as that described for the experimental group without exposure to the exergame; they will read 3 times a week for 15 to 20 minutes instead of engaging with our exergames. To maintain consistency between the control and experimental conditions, the same questionnaires and surveys will be completed by all the participants in both groups, except for the *perceived enjoyment* and *rate of perceived exertion (RPE)* scales, which will be completed only by the experimental group. Both qualitative and quantitative methods will be used to provide pilot data on potential outcomes of interest. Although this study will evaluate the feasibility of both the study intervention and study control arms, we will not randomize the participants. Participants in the intervention arm will be recruited first, followed by a wave of participants recruited to the control group. The study is based in Waterloo but will be carried out remotely, so participants from across Canada will be eligible.

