### Study Sample and Recruitment

A combination of convenience and snowball sampling will be used for the purposes of this study. To be eligible, participants must be aged ≥60 years, living in a community setting in Canada, and able to communicate in English and provide consent on their own behalf. The participants must have access to a computing device (computer or tablet) and a reliable internet connection at their place of residence to complete the web-based assessments and tasks. Participants in both groups must be able to safely participate in light to moderate unsupervised activity without requiring a physician’s approval as assessed using the Get Active Questionnaire (GAQ) [55,56]. Exclusion criteria include (1) diagnosis of moderate or severe dementia or a score <18 on the Montreal Cognitive Assessment (MoCA; version 8.1-Telemed) [57,58]; (2) self-reported severe motion sickness or commonly experienced motion sickness or nausea when driving or sitting in a car, train, or bus; (3) self-reported hearing impairment that may interfere with the participant’s ability to hear and understand the auditory cues in the cognitive and perceptual tasks; (4) uncorrected visual impairment (eg, cataracts, glaucoma, or macular degeneration) that may interfere with the participant’s ability to see and interact with the game and perform the cognitive and perceptual tasks; (5) ear infection in the previous 12 months or a diagnosis of a disease of the middle ear, such as Meniere disease; and (6) any preexisting conditions that would prevent them from engaging in exercise, including having a cardiac pacemaker. The same inclusion and exclusion criteria will be used for both the experimental and control groups to ensure internal validity.

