#### Demographics

Background and demographic data will be obtained through (1) a demographic questionnaire, (2) the remote MoCA (version 8.1-Telemed) [58], and (3) the short version of the Geriatric Depression Scale-15 (GDS-15) [63]. The demographic questionnaire is developed by the research team and collects basic information of the participants (eg, age, sex, gender, and education), their health (eg, perceived physical and mental well-being, history of falls, and hearing and vision impairments), and previous experiences with gaming and motion sickness. The MoCA is a validated screening tool for cognitive impairment with high sensitivity and specificity for detecting mild cognitive impairment and dementia [57]. The MoCA will not be used for diagnostic purposes but will be used by the researchers to gain insight regarding the sample’s baseline cognition (a MoCA score of <13 suggests severe cognitive impairment; this study will use a cutoff score of ≥18 for study inclusion). The remote audiovisual administration of the MoCA will be conducted by a trained researcher. The GDS-15 is a widely used depression assessment tool that is specifically designed for older adults. Similar to the MoCA, the purpose of using the GDS-15 is to gain insight into the sample’s baseline depressive symptoms (if any). The GDS-15 consists of 15 questions about how the participant has felt over the previous week.

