#### Executive Function

Cognitive data from the OTMT (completion time [seconds] for parts A and B separately) and VF (the number of unique animal names) will be analyzed for within-participant and between-participant variables. For the modified flanker task, the participants’ mean RT and proportion error (1-accuracy) for each block of flanker responses will be obtained and further separated by congruence (congruent, incongruent, and neutral). Incorrect responses, responses that occurred 1000 ms after stimulus onset, and double responses for a single stimulus will be considered as errors and excluded from the analysis. The rate of no response and gender will be included as covariates.

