#### Exploratory Analysis

To better understand the relationship between lower-level perceptual processing and multisensory integration (assessed via the RT, SIFI, SJ, and TOJ tasks) and higher-order executive function (assessed via the modified flanker task, VF, and OTMT), exploratory correlational analyses will be conducted between the outcomes of each of the perceptual tasks (eg, TBW, point of subjective simultaneity, mean RT from the multisensory and unisensory conditions, and accuracy) and the outcomes of the modified flanker task (accuracy and mean RT), VF, and OTMT. Furthermore, exploratory analyses using correlations are planned using both game metrics and cognitive assessments (ie, modified flanker and RT tasks) for RT. Partial correlation analyses, including age, sex, and previous experience with video games as covariates, will be applied when appropriate. Correlational analyses will be conducted for outcome variables obtained before and after 6 weeks of the exergame intervention and before and after acute bouts of engagement with the exergame. The Bonferroni correction will be used to correct for multiple comparisons.

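### The stated flanker covariates leave out age in a comparison of two non-randomised waves, exposing the group main effect and the independent t tests to confounding by age; the time-by-group contrast is exposed only if age affects change

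*Protocol article*

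**What the plan says.** All references are to the protocol article.

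- **Covariates.** Under Executive Function in the Statistical Analysis Plan, the flanker paragraph ends: "The rate of no response and gender will be included as covariates". Age is not listed.
- **Allocation.** Study Design says "we will not randomize the participants" and "Participants in the intervention arm will be recruited first, followed by a wave of participants recruited to the control group".
- **Who enters.** Under Study Sample and Recruitment, sampling is by convenience and snowball, and "participants must be aged ≥60 years"; no upper limit is given. The stated safeguard for comparability is common eligibility: "The same inclusion and exclusion criteria will be used for both the experimental and control groups to ensure internal validity". No matching or balancing on age is described.
- **Age is available.** Under Demographics, the baseline questionnaire "collects basic information of the participants (eg, age, sex, gender, and education", among other items).
- **Arm comparisons.** Outcome Analyses plans paired and independent two-tailed t tests of baseline, follow-up and acute scores, and repeated-measures and mixed ANOVAs with time, group and day as factors.
- **Age elsewhere.** Exploratory Analysis says "Partial correlation analyses, including age, sex, and previous experience with video games as covariates, will be applied when appropriate". This concerns correlations, not an arm comparison.

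**The concern.** Randomisation would make age differ between arms only by chance. Here the arms are self-selected groups recruited one after the other, so a systematic age difference is possible, and shared eligibility criteria with an open upper age limit do not rule it out. The flanker task yields response times and error rates, and the article's own introduction is built on age-related cognitive change. If age is related to the score and differs between waves, an unadjusted comparison of levels attributes part of the age difference to exergaming.

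This is more than a detail left to a fuller plan. The article chose to state a covariate set for this outcome, and that set adjusts for gender but not for age, without giving a reason. At stake are the flanker between-group results. The Sample Size section says the study should inform sample size calculations for a larger trial, so an age-confounded arm difference could be carried into that planning.

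**Working it through.** **Nothing to reproduce.** The article states no SD, effect size, correlation or power for the flanker task, and says that no formal sample size calculation is made. The figures below are illustrations.

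**Input from the article:** at least 12 per group, hence 12 + 12 − 2 = 22 degrees of freedom for an unadjusted two-group test.

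**Assumed inputs:** age SD 7 years within each wave; correlation r between age and the flanker score of 0.2 to 0.5; two-sided alpha 0.05; no true effect.

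**Step 1: bias in a comparison of levels** (independent t test at follow-up, or group main effect).

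Bias in SD units = r × (difference in mean age / 7). The noncentrality of the t test is bias × √(12/2) = bias × 2.449, and the rejection rate follows from the noncentral t with 22 df.

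| Systematic age difference | r | Bias (SD) | Noncentrality | Rejection rate |
|---|---|---|---|---|
| 3 years | 0.2 | 0.2 × 3/7 = 0.09 | 0.21 | 5.5% |
| 3 years | 0.5 | 0.5 × 3/7 = 0.21 | 0.52 | 7.9% |
| 5 years | 0.2 | 0.2 × 5/7 = 0.14 | 0.35 | 6.3% |
| 5 years | 0.5 | 0.5 × 5/7 = 0.36 | 0.87 | 13.3% |

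**Step 2: bias in the time-by-group contrast.** This contrast compares before-to-after change between arms. In SD units the bias is (r after − r before) × standardised age difference. If the age slope is the same before and after, the bracket is zero and the bias vanishes.

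**Step 3: simulation of both contrasts.** Assumed: 12 per arm, no true effect, before/after correlation 0.7, age difference 0.5 or 1.0 SD, r of 0.3 or 0.5. Ranges run across these scenarios.

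| Contrast | Bias (SD) | Type I error |
|---|---|---|
| Follow-up t test, no age, constant age slope | 0.15 to 0.50 | 6.5% to 21.8% |
| Group main effect, no age, constant age slope | 0.15 to 0.50 | 6.9% to 24.6% |
| Time by group, no age, constant age slope | about 0 | 4.7% to 5.1% |
| Time by group, no age, slope shifts by 0.1 | 0.05 to 0.10 | 5.2% to 6.3% |
| Follow-up with age as covariate (constant or shifting slope) | −0.01 to 0.02 | 4.4% to 5.5% |

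The upper figures in the first two rows need an age difference of a full SD (7 years under the Step 1 assumption) together with r = 0.5.

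**Step 4: why the interaction is needed.** With complete before and after data, an age main effect alone adjusts the group main effect but leaves the time-by-group contrast unchanged, because it drops out of within-person change. Only an age-by-time term protects that contrast when change depends on age.

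**The case against.** **The main contrast is largely protected.** A reader might infer that any age difference between the waves passes directly into every arm comparison. The documents do not support that. Time is a factor in the planned mixed ANOVAs, so each participant's before score removes a constant age effect from the time-by-group contrast. This stands, and it limits the point to the group main effect and the independent t tests, plus change that depends on age. An acute comparison made on before-to-after change is protected in the same way; one made on the scores themselves is not.

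**Chance imbalance proves nothing.** With 12 per arm, chance alone often produces a noticeable age difference, which might seem to show inflated error rates. It does not: the standard error of an unadjusted test already covers chance imbalance. Only a systematic difference inflates the error rate, and the article gives no evidence that one exists. This stands; the risk comes from the design and has not been shown to occur.

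**The article does not contradict itself.** The use of age under Exploratory Analysis might be read as conflicting with the flanker covariates. It applies to partial correlations, where appropriate, so it shows at most that age was thought relevant there.

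**Other outcomes and the choice of gender.** A reader might extend the point to the Oral Trail Making Test, verbal fluency and response time task, for which no covariates are named. That silence is ordinary in a condensed article and is no error. Nor do the documents rank age above gender, so replacing gender would be a preference.

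**Low stakes.** The flanker task is secondary, the study's primary purpose is feasibility and usability, and Strengths and Limitations already asks for cautious interpretation. The baseline description would also allow an age difference to be seen. All true, but seeing an imbalance does not adjust for it, and none of this is a reason to leave age out.

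**Conclusion.** The point holds in limited form. The stated flanker covariates omit a measured potential confounder in a non-randomised, sequential comparison. If the waves differ systematically in age, the group main effect and the independent t tests of follow-up and acute scores are biased: by 0.14 to 0.36 SD for a 5-year difference, assuming an age SD of 7 years and a correlation of 0.2 to 0.5. The time-by-group contrast is biased only if age affects change, and then modestly in the scenarios tried (0.05 to 0.10 SD for an assumed slope shift of 0.1).

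The age SD, correlations, age differences and slope shift are all assumptions; the documents establish only that the bias could arise, not its size. Severity is low: a worthwhile refinement, not a flaw that threatens the study's feasibility aims.

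**What to change.** Under Executive Function, extend the flanker arm-comparison model to include age, centred, with its interaction with time, alongside gender and the rate of no response. State that between-group conclusions on the flanker task rest on that adjusted model and its time-by-group term, and not on unadjusted independent t tests at follow-up. The second sentence matters because those t tests take no covariates, so changing the ANOVA model alone would leave them exposed.

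The cost is analysis wording only, since age is already collected, plus about one or two of roughly 22 between-person degrees of freedom. Adjustment removes confounding by age only as far as the assumed linear relation holds, and does nothing for other differences between the waves.

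Using the same age term in the Oral Trail Making Test, verbal fluency and response time arm comparisons would be consistent, but is only a suggestion.

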#### Multisensory Integration

##### SIFI Task

Analyses will be conducted to determine whether there are differences in before and after intervention (exergaming or reading for 6 weeks) data as well as for before and after acute (1 bout of exergaming or reading) data. Analyses will be conducted separately on the proportion correct for unimodal (modality: vision-only or auditory-only) and multimodal (audiovisual conditions: nonillusory, 1 flash and 1 beep or 2 flashes and 2 beeps; or illusory, 1 flash and 2 beeps) conditions. To examine changes in susceptibility to the SIFI, sensitivity (*d*) will be calculated (*z*[hits] − *z*[false alarms]) for each SOA, and appropriate analyses will be conducted [96-98].

##### SJ and TOJ Tasks

To estimate the accuracy (point of subjective simultaneity) and precision (TBW) with which the participants make their judgments for the SJ and TOJ tasks, psychometric functions will be fitted to each participant’s responses as a function of SOA. To investigate the relationships between TBWs obtained from the 2 tasks and not their absolute size, the *b* values (ie, SD) of these psychometric functions will be analyzed as a proxy for the size of the TBW to avoid discrepancies in the literature that differ when defining the absolute size of the TBW [99-101]. Each task will be analyzed individually for each participant, with participant data fitted to both Gaussian and logistic functions.

##### RT Task

Data trimming procedures will not be applied [99,102]; however, responses faster than 100 ms and slower than 1500 ms will be set to infinity rather than excluded [99,103] where this method of data trimming was used. The mean RT for each modality (auditory, visual, or audiovisual) before and after the experimental and control conditions will be calculated individually for each participant, and appropriate analyses will be conducted to determine the impact of time and modality. Acute data (before and after exergaming or reading) will also be analyzed as described previously.

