For the SIFI task, there will be 3 conditions: vision-only, auditory-only, and audiovisual. In the vision-only block, 2 flashes will be presented, and the participant’s task will be to indicate the number of flashes they saw. In the auditory-only block, 2 beeps will be presented, and the participants will be asked to indicate the number of beeps they heard. There will be 30 trials in each of the unimodal conditions (SOAs: 70 ms, 150 ms, and 230 ms). The audiovisual trials will consist of 2 control conditions (1 beep and 1 flash and 2 beeps and 2 flashes) as well as the illusion condition (2 beeps and 1 flash). In the audiovisual control conditions, the auditory and visual stimuli will be presented simultaneously. In the 2 beeps and 1 flash (illusory condition) auditory-led trials, the auditory stimulus will be presented first, after which the auditory and visual stimuli will be presented simultaneously following a variable SOA. In the 2 beeps and 1 flash vision-led trials, the first auditory stimulus will be accompanied by a visual stimulus, and the second auditory beep will follow a variable SOA. The 3 audiovisual conditions will be randomly presented within the testing block to avoid response bias. The participants will be asked to fixate on the fixation cross for the duration of the task, report the number of flashes seen, and ignore the auditory stimuli. All conditions will be repeated 10 times for a total of 100 trials (including 10 repetitions for 0 SOAs, where a single beep and flash will be presented simultaneously). In total, 160 trials, as well as additional practice trials, will be presented for all 3 conditions (vision-only, auditory-only, and audiovisual). This task will take approximately 5 to 10 minutes to complete.

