For the SJ task, the participants will be instructed to report, using the number *1* and *2* keys on their keyboard, whether they perceived the auditory and visual stimuli as occurring simultaneously (number *1* key) or not (number *2* key). A total of 10 trials will be presented in a randomized order for each SOA, and 6 practice trials will also be presented for a total of 76 trials. This task will take approximately 5 to 10 minutes to complete. The experimental design of the TOJ task will be identical to that of the SJ task with the exception of the task instructions. In this case, the participants will be asked to report, using the number *1* and *2* keys on their keyboard, whether they perceived the visual (number *1* key) or auditory (number *2* key) stimulus as appearing first.

For the RT task, the participants will be told that they will see a flash of light, hear a beep, or a combination of the 2, and they will be instructed to press the response button (space bar key) as soon as they detect any of the 3 experimental conditions. Each condition will be presented 50 times in a random order with 6 practice trials for a total of 156 trials. However, if a participant responds too quickly (<100 ms) or takes longer than 3 seconds to respond to a trial, that trial will be repeated. This task will take approximately 5 to 10 minutes to complete.

Both the multisensory integration and modified flanker tasks will be designed using PsychoPy (Open Science Tools Ltd) and distributed on the web using Pavlovia (Open Science Tools Ltd), wherein the participants will be provided with URLs to access the tasks. All instructions will be embedded within the tasks and will not require the presence of a researcher to be completed. However, a researcher will join the participants for the duration of the first session of these tasks to ensure that all inquiries and technical difficulties are resolved as soon as they arise. Furthermore, 1 to 2 members of the research team will check in with the participants every 2 weeks to answer any questions and ensure that they are following the protocol.

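### The RT task codes out-of-window responses as infinity and then averages them, so one accepted slow response makes that modality-by-session mean infinite

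*Protocol article*

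**What the plan says.** The analysis section headed RT Task opens with "Data trimming procedures will not be applied". The same sentence continues that "responses faster than 100 ms and slower than 1500 ms will be set to infinity rather than excluded". The next sentence defines the outcome: "The mean RT for each modality (auditory, visual, or audiovisual) before and after the experimental and control conditions will be calculated individually" for each participant.

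The task description under Multisensory Integration fixes the amount of data: "Each condition will be presented 50 times in a random order with 6 practice trials for a total of 156 trials". It also fixes what is re-run at collection: "if a participant responds too quickly (<100 ms) or takes longer than 3 seconds to respond to a trial, that trial will be repeated".

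Outcome Analyses compares baseline, follow-up and acute scores by paired and independent t tests and by repeated-measures and mixed ANOVAs. Exploratory Analysis correlates mean RT from the unisensory and multisensory conditions with the executive function measures.

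**The concern.** Coding an outlying response as infinity is sensible when the target is a cumulative RT distribution or a quantile: the trial still counts in the denominator, and its exact value does not matter. The article describes no such analysis. The only participant-level RT summary it names is an arithmetic mean, and a mean has no tolerance for an infinite value.

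Followed literally, the plan would give some participants an infinite RT score in some cells, and group comparisons involving those cells would return nothing. In practice someone would repair this at analysis by dropping the trials, dropping the participants or abandoning the rule. Those repairs give different answers. They bear most on the slowest responders and could differ between before and after or between groups. An unplanned choice made with the data in view is what a stated rule should prevent.

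**Working it through.** **Inputs from the article**
- 50 trials per modality per session, three modalities, 6 practice trials (Multisensory Integration). Check: 3 × 50 + 6 = 156, the stated total.
- Trials repeated at collection: under 100 ms or over 3 s (same section).
- Values coded as infinity: under 100 ms or over 1500 ms (RT Task).
- At least 12 participants per group (Sample Size).

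**Input not in the article**
- The share q of accepted responses between 1.5 and 3 s. Assumed range: 0.1% to 2%.

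**Step 1: which responses become infinite.** Responses under 100 ms or over 3 s have already been repeated. What remains in the data and meets the infinity rule is the band from 1.5 to 3 s.

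**Step 2: effect on one mean.** With 49 finite values and one infinite value, (finite sum + ∞)/50 = ∞, and the SD involves ∞ − ∞, which is undefined. In a simulated set of 50 RTs (finite mean about 397 ms, median 402.6 ms), recoding one value to infinity gave an infinite mean, an undefined SD and an unchanged median.

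**Step 3: effect on the tests.** With one infinite mean among 12 participants, both the paired and the independent t test returned an undefined statistic and p value. If a participant's before and after means are both infinite, the change score is ∞ − ∞, also undefined.

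**Step 4: does another rule rescue it?**
- Exclusion is ruled out by the wording itself.
- The log transformation in Outcome Analyses does not help, since log(∞) = ∞.
- Handling of Missing Data does not apply, because an infinite value is not missing.
- No median, quantile or cumulative-distribution analysis of RT is described.
- The other RT measures are handled differently: late flanker responses are excluded (Executive Function), and fishing RTs outside 100 to 1000 ms are discarded (Gameplay Metrics).

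**Step 5: how often.** Chance of an infinite mean in one modality and one session: 1 − (1 − q)^50. Chance that at least one of 12 participants is affected in that same cell: 1 − (1 − q)^600. Both treat trials as independent with a common rate.

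| Assumed q | One participant, one cell | At least one of 12 |
|---|---|---|
| 0.1% | 4.9% | 45% |
| 0.5% | 22% | 95% |
| 1% | 39% | 99.8% |
| 2% | 64% | about 100% |

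**Step 6: the choice of repair matters.** Suppose 49 responses average 400 ms (an illustrative level) and one lies between 1500 and 3000 ms. The in-window mean is 400 ms. The mean of all accepted responses is between (49 × 400 + 1500)/50 = 422 ms and (49 × 400 + 3000)/50 = 452 ms. The rule as written gives infinity.

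**The case against.** The strongest reply is that the sentence is visibly condensed. It disclaims trimming, gives a cut-off, then calls the cut-off a trimming method with reference to cited work. The authors may intend an in-window mean, with the infinity convention meant for a distributional analysis in a fuller plan. That is plausible, and it argues against forecasting that the trial will lose this outcome. It does not make the published rule workable: a fuller plan can add detail, but it would have to change one of these two sentences.

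The reply is right on scale. RT is one of four perceptual tasks within one secondary domain of a non-randomised feasibility pilot, and no primary outcome uses it.

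Three stronger readings are tempting, and the document does not support them.
- *One slow trial destroys all of a participant's RT data.* It spoils one modality in one session. Pooling three modalities over two sessions (300 trials) at an assumed 1% gives 1 − 0.99^300 = 95%, or about 11 of 12 participants, but that is the chance that any one of six means is hit. Slow responses probably also cluster in a few people, which would lower the number of participants affected.
- *The 3 s and 1500 ms limits contradict each other.* One governs re-running trials at collection and the other governs analysis. A wide collection limit with a narrower analysis limit is coherent. The gap matters here only because of the infinity rule.
- *The SIFI sensitivity index has the same fault,* because with 10 trials per SOA a proportion of 0 or 1 has no finite z value. The arithmetic is right, but the formula is standard and the article prescribes no infinite value. The correction for extreme proportions is routine detail that an article leaves to the full plan.

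**Conclusion.** The point holds for the RT task as written. That one infinite value makes a modality-by-session mean infinite, and leaves the planned tests on it undefined, needs no assumption. How often this would happen does: about 5% to 64% per participant, modality and session for assumed rates of 0.1% to 2%, with independent trials and a common rate. The article gives no rate. Even at the lowest assumed rate there is a 45% chance that at least one of 12 participants in a group is affected in a given cell, and one is enough to stop the test. This is a wording error with a real consequence for one secondary outcome. It should be corrected before analysis, and it does not threaten the pilot's feasibility conclusions.

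**What to change.** Replace the two sentences under RT Task with one of the following, chosen before the RT data are analysed:

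1. **Median.** Summarise RT by the median per participant, modality and session. Any response above 1.5 s already lies above a typical median, so coding it as infinity changes nothing, and with 50 trials the median stays finite with up to 24 infinite values. The cost is slightly lower efficiency than the mean when the data are clean.
2. **In-window mean.** Keep the infinity coding for cumulative RT distributions only, and compute the mean over responses of 100 to 1500 ms. Report the proportion of out-of-window responses by group and time point. The cost is that the slowest trials leave the mean, which is why that proportion must be shown beside it.

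Carry the chosen summary into Outcome Analyses and Exploratory Analysis so that the t tests, ANOVAs and correlations use the same quantity, and remove the statement that no trimming is applied if option 2 is taken. Either option takes a sentence or two and needs no new data.

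### Response-time trials coded as infinity are kept and then averaged, so any response of 1500 to 3000 ms makes that participant's mean RT infinite and the stated tests unusable

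*Protocol article*

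**What the plan says.** The RT Task paragraph of the analysis plan opens with "Data trimming procedures will not be applied". It then sets the handling of out-of-window responses: "responses faster than 100 ms and slower than 1500 ms will be set to infinity rather than excluded". The next sentence fixes the participant-level outcome: "The mean RT for each modality (auditory, visual, or audiovisual) before and after the experimental and control conditions will be calculated individually for each participant". No median, quantile, cumulative-distribution or finite-values-only step is named.

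Three other places bear on this:

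- **Task description (Multisensory Integration, under Outcomes and Measures).** "Each condition will be presented 50 times in a random order with 6 practice trials for a total of 156 trials". A repeat rule applies during collection: "if a participant responds too quickly (<100 ms) or takes longer than 3 seconds to respond to a trial, that trial will be repeated".
- **Outcome Analyses.** Baseline, follow-up and acute scores are compared by paired and independent t tests and by repeated-measure and mixed ANOVAs. Log transformation is the remedy for skew.
- **Exploratory Analysis.** The correlations take in "mean RT from the multisensory and unisensory conditions". The type of correlation is not stated.

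**The concern.** Setting a response to infinity is a sound device when the summary depends only on order, as a median, a quantile or a cumulative distribution does. It says that the response was slower than anything observed without fixing a value. It does not work with an arithmetic mean, because one infinite value makes the whole mean infinite. The plan states both the code and the mean, and it rejects the step (exclusion) that would make them compatible.

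Once a trial is coded, the analyst has to depart from the text after seeing the data. The choices are to drop the coded trials, which the plan says it will not do, to drop the participants who have them, or to change the summary. With about 12 people per group, that choice can move the result. The pilot is also meant to inform the sample size of a larger trial, and for this measure that needs finite means and standard deviations.

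**Working it through.** **Inputs from the protocol article**

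- Trials per modality per session: 50. Check of the stated total: 3 × 50 + 6 practice = 156, which agrees.
- Analysis window: 100 to 1500 ms. Repeat limits at collection: under 100 ms and over 3 s.
- Planned size: at least 12 per group.
- Share of trials coded infinite: not given. The values of p below are assumptions.

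**Step 1. Which responses are exposed**

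| Response | At collection | At analysis |
|---|---|---|
| under 100 ms | trial repeated | infinity, if the original is kept |
| 100 to 1500 ms | accepted | used as measured |
| 1500 to 3000 ms | accepted | infinity |
| over 3 s | trial repeated | infinity, if the original is kept |

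The text does not say whether a repeat replaces the original. If it does, only the 1500 to 3000 ms row is left to be coded. That row is exposed under either reading.

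**Step 2. What one coded trial does**

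Fifty RTs were simulated for each of 12 people (assumed normal, mean 350 ms, SD 60 ms), and one trial of one person was set to infinity. For that person:

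- mean of the 50 trials: infinite
- median of the 50 trials: 351.9 ms
- mean of the 49 finite trials: 347.4 ms, against 347.8 ms for all 50 before coding

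With that person among the 12, the paired t test, the independent t test and the Pearson correlation all return no value. The log of the score is still infinite. If both occasions are affected, the change is infinity minus infinity, which is undefined. A Spearman correlation does run and ranks that person slowest.

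**Step 3. How often this would happen, with independent trials and one common rate**

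- Chance that one 50-trial mean is infinite: 1 − (1 − p)^50.
- Chance that a baseline to follow-up paired t test for one modality in 12 people contains an infinite value: 12 × 2 × 50 = 1200 trials, so 1 − (1 − p)^1200.

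| Assumed p | One mean infinite | Paired test affected |
|---|---|---|
| 0.05% | 2.5% | 45.1% |
| 0.1% | 4.9% | 69.9% |
| 0.2% | 9.5% | 90.9% |
| 0.5% | 22.2% | 99.8% |
| 1% | 39.5% | over 99.9% |
| 2% | 63.6% | over 99.9% |

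**Step 4. If slow trials cluster in a few people**

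Let each person's rate follow a beta distribution with mean 1% and shapes a and 99a (assumed). A person keeps a finite before-after pair for one modality when none of 100 trials is coded.

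| Model, mean rate 1% | Chance of a finite pair | Expected finite pairs of 12 | Chance that at least one of 12 is infinite |
|---|---|---|---|
| Common rate | 0.99^100 = 0.366 | 4.4 | over 99.9% |
| Beta, a = 0.5 | 0.574 | 6.9 | 1 − 0.574^12 = 99.9% |
| Beta, a = 0.1 | 0.783 | 9.4 | 1 − 0.783^12 = 94.7% |

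Clustering more than doubles the number of usable pairs in the last row, yet the test as written still almost always meets an infinite value.

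**The case against.** The strongest reply is that the exposure is narrower and less certain than the arithmetic suggests.

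- **The repeat rule removes most bad trials.** This largely stands. A reader might infer that the problem holds whatever window is chosen. The documents do not support that: if repeats replace originals and the analysis window were 100 ms to 3 s, no trial would be left to code and every mean would be finite. The difficulty is therefore tied to the mismatch between 1500 ms and 3 s.
- **The percentages rest on assumptions.** This stands. No rate is given, the task is a simple key press on detection, and the common-rate model overstates how many participants are affected if slow trials cluster. It would also be inconsistent to use that model and argue that the slowest people are the ones lost.
- **The correlations might still run.** This stands in part. The exploratory section names no correlation type, and a rank correlation tolerates an infinite score. Only a Pearson correlation fails.
- **The wording may be limited by its sources or completed in a fuller plan.** The sentence ends with an unclear clause about where this method was used, and the article promises corrective procedures if needed. But the clause names no analysis in this study to which the code is confined, and the corrective procedures are tied to statistical assumptions. The code and the mean are both stated, so this is a conflict in the text and not an omitted detail.
- **The failure is visible.** True: software returns an infinite or missing result, so it would not silently give a wrong answer. The harm is an unplanned choice made after the data are seen.

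**Conclusion.** The point holds in limited form. The infinity code and the mean RT cannot both be applied once a single trial is coded; that conclusion needs no assumed rate. How often it occurs does need one. For 0.2% to 2% of trials coded, independently and equally across people, 10% to 64% of 50-trial means are infinite. With clustering the share of participants is lower, but one affected participant is enough to stop a t test or ANOVA.

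A reader might infer that the trial's main results are at risk. They are not. RT is one of four perceptual tasks within one of five secondary domains, in a non-randomized pilot whose primary outcomes are feasibility and usability. No feasibility outcome depends on mean RT. The correction should be made, but it is not a condition for the study to proceed.

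**What to change.** Change the RT Task paragraph, and the mean RT terms in Exploratory Analysis, in one of two ways.

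**(a) Median.** Use the median RT per modality, participant and occasion. Code only slow responses as infinite. Exclude responses under 100 ms or replace them by the repeated trial; coding them as plus infinity would rank an anticipation as the slowest response and push the median up. The median stays finite while fewer than half of the trials are coded.

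**(b) Mean.** Keep the mean, over in-window trials only. Replace both the no-trimming statement and the words that reject exclusion with that rule. Changing only one of them leaves the sentence contradicting itself.

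In either case, report the number of coded or excluded trials by group and occasion. Also align the 1500 ms analysis limit with the 3 s repeat limit in the task description, and say whether a repeated trial replaces the original.

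The cost is a sentence or two in each place and no new data. A median is slightly less efficient than a mean of clean data.
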